## Methods

### Participants and Procedure

The pilot study is being implemented in the German city of Chemnitz. Chemnitz is the third-largest city in the federal state of Saxony in the southeastern part of Germany, with a population of 250,398 (in 2023) [42]. In 2022, nearly 30% of the population of Chemnitz was aged 65 years or older; 15% were aged 75 years or older [43]. In 2020, Chemnitz was the city with the highest median age in Europe (52 years) [44]. Forecast calculations expect that by 2030, the Chemnitz region will have the highest share of people aged 65 years or older (nearly 38%) in Europe [1]. According to population forecasts, the share of Chemnitz residents aged 80 years or older will also rise from 8% in 2018 to nearly 11% in 2030 [45]. Due to these demographic developments, there is an urgent need for target group-specific and low-threshold community health promotion programs (eg, PA interventions) to support the healthy aging of vulnerable older adults who live in the city of Chemnitz. This city was furthermore chosen due to its immediate proximity to the Technical University of Chemnitz, which is conducting the study, and its collaboration with the city of Chemnitz’s health department, as well as support from various local partners (eg, citizen platforms).

The aim during the study period is to cover at least 4 out of 39 districts in Chemnitz, representing the city’s average demographic age (>50 years) and lower socioeconomic districts (compared to the city of Chemnitz’s average) [46,47]. The recruitment of participants is planned primarily due to collaboration with local partners. Announcements will be conducted in different communal facilities for older adults (eg, citizen online platforms, assisted living facilities, and citizens’ meeting points) through flyers, at information events, in institutional newspapers, and in the personal conversations of the research team with targeted older adults as well as with staff of different social institutions. The study will be announced in various local and district newspapers, and flyers will be distributed in shops, for example, in bakeries and pharmacies. Additionally, older adults who had participated in previous studies and had consented to being informed about future studies will be contacted.

Eligibility to participate in the study will be determined in personal interviews by qualified staff based on the inclusion and exclusion criteria described below.

### Inclusion and Exclusion Criteria

The study primarily targets older adults aged 75 years or older who can be considered vulnerable (eg, poverty, loneliness, physical restrictions, and a low level of education) and who reside in the city of Chemnitz.

Residents are eligible to participate in the study if they (1) have at least basic knowledge of the German language, (2) can independently travel to the assessment and intervention locations, which will be meeting points in close proximity to their home, and (3) provide informed consent to participate in the study.

Participants will be excluded from the study if they have a medical condition preventing them from engaging in regular PA or if they had a severe adverse health event within the last 6 months (eg, myocardial infarction, stroke, fracture, surgery, or pneumonia) to ensure their safety during the PA sessions. Additionally, participants will be excluded if they participate in other clinical trials as well as in regular PA programs at least twice a week (eg, regular gym visits or rehabilitation exercise programs) to address older adults who are less physically active and to analyze solely the impact of the intervention.

### Study Design

The pilot study is designed as a population-based prospective observational cohort study and is being carried out in 4 different districts in the city of Chemnitz. The first screening for study eligibility will be assessed through a standardized telephone interview with, for example, questions about older adults’ age, health conditions, and regular weekly PA exercises. Afterwards, participants will complete an assessment conducted by the research team in their direct neighborhood (eg, in the facilities of community centers), which includes questionnaires and objective measurements of physical and cognitive function and of psychosocial health. In addition to these measurements, participants will wear a pedometer for 7 consecutive days to assess their PA behavior. Measurements will take place at 3 different time points over an 18-month period, namely at the beginning (T1), at the end (T2), and 6 months after the end of the intervention (T3) (Figure 1).

The project was launched in October 2021 and will be completed in September 2025. The first participants were recruited in August 2022.

**Figure 1 figure1:**
[figure not shown]
Study flow of the population-based prospective observational cohort study BeTaSen (Bewegungs-Tandems in den Lebenswelten Chemnitzer Seniorinnen und Senioren: ein Beitrag zur kommunalen Gesundheitsförderung) with a study population of older adults (aged 75 years or older) living in Chemnitz, Germany. *Outcome evalution. **Process evaluation.

### Design and Organization of a Physical Activity–Promoting Intervention

All participants will participate in the target group-specific community-based PA intervention. The pilot study’s intervention period is 12 months per participating neighborhood. The participants will be encouraged to continue to engage in PA independently (Figure 2).

The intervention’s main component will comprise regular PA meetings organized in so-called “activity tandems,” which take place once a week for 30-45 minutes. One activity tandem will include 1 trained voluntary mentor and 3-4 older adults living in the same neighborhood. These activity tandems will primarily engage in low-threshold outdoor PA and exercise together in their neighborhood. For this, easily accessible locations such as urban lawns, walking paths, parks, and fitness trails will be used. In case of bad weather, the PA meetings will be organized in the meeting places of collaborating partners, for example, community centers. Due to the small group size, the content of each tandem lesson can be flexible and tailored to the individual participant’s needs. For example, the exercises can be performed at different levels of intensity, or alternative exercises can be selected from a large PA-exercise pool. Additionally, monthly group meetings (eg, 3-4 activity tandems with a total of 12-16 older adults) will be organized in each neighborhood district in the intervention months 5-12 (Figure 2), which will be delivered by trained exercise instructors. In these group meetings, in addition to PA exercises, the following contents will be covered: knowledge about the positive effects of PA, goal setting and planning, barrier management, and motivational aspects, as well as the sustainable implementation of regular PA in everyday life. Measures like small group sizes, qualified mentors, support material (eg, first aid kits, pulse oximeters, Borg scales), and the accessible, familiar environment of the activity sessions ensure the safety and well-being of participating older adults.

**Figure 2 figure2:**
[figure not shown]
Procedure of the population-based prospective observational cohort study BeTaSen's intervention over a period of 12 months; an example is shown for 1 district (study population: older adults aged 75 years or older living in Chemnitz, Germany). BeTaSen: Bewegungs-Tandems in den Lebenswelten Chemnitzer Seniorinnen und Senioren: ein Beitrag zur kommunalen Gesundheitsförderung).

In total, around 6-8 activity tandems will be created in each of the 4 local districts (approximately 24-32 older adults per district). Thus, the goal is to reach a total of approximately 120 older adults residing in the city of Chemnitz during the project period.

Voluntary mentors (eg, volunteers from Chemnitz, students, and community center staff) will be recruited through various public channels (eg, newspapers, flyers, and mailing lists) in cooperation with municipal partners. The trained mentors should guide the activity tandem groups (eg, demonstrate PA exercises with the help of the manual and walk paths), ensure safety and well-being (eg, through individualized feedback), and encourage the older adults to do independent regular PA exercises. The mentors will also be responsible for communication and the planning of the activity tandem meetings. Researchers on the project team will instruct mentors in a workshop about how to conduct PA meetings, how to appropriately deal with the target group, and how to perform basic first aid procedures. In addition, mentors will be equipped with support materials, such as a manual that includes a range of various low-threshold PA exercises, an overview of district walkways, and additional exercise materials (eg, resistance bands and everyday objects).

The mentors will supervise and support the activity tandems once a week initially at the start of the intervention (intervention months 1-4), later once every 2 weeks (intervention months 5-6), and then once a month (intervention months 7-9). The older adults will thus be gradually encouraged to independently engage in weekly PA activity meetings, as from intervention month 10 onward, they will be prepared for basically independent implementation. Furthermore, older adults will be encouraged to actively participate in the activity tandems, for example, by choosing walkways or suggesting individual exercises. During the intervention period, participants will be given exercise material (eg, brochures) to continue regular PA in their activity tandem and on their own. To ensure that older adults do not overexert themselves as well as to enable them to get a better sense of their exercise limits, their oxygen saturation and heart rate (using a pulse oximeter; Orbisana Healthcare GmbH) as well as a subjective exertion rate (based on the Borg scale; [48]) will be measured at the beginning, middle (during physical exertion), and end of each activity tandem meeting. Based on these measures, participants will receive direct feedback, and the PA exercise intensity can be adjusted individually.

In line with previous literature and findings, the vulnerable target group’s potential barriers should be carefully considered when developing the pilot study. To ensure low-threshold accessibility, the activity tandems and monthly group meetings will take place in the older adults’ neighborhoods. District plans will be drawn up to identify sitting areas and public toilets, for example, and to pinpoint accessible walkway plans. The activity tandem’s PA content will be designed to reflect daily life activities in a very playful, individualized, ability-oriented, and motivational way. Each unit can be freely designed by the mentors and older adults based on the PA, exercise materials, and recommendations provided. Each activity tandem unit should begin with a warm-up, and the components of strength, endurance, coordination, stretching, and relaxation should be addressed regularly in different sessions. In addition, the mentor should include knowledge transfer in each unit, for example, about the positive effects of PA. Moreover, participation in the PA intervention does not entail any financial costs (eg, materials and participation fees). To promote sustainable participation in the neighborhood meetings and to ensure that the PA meetings are tailored to the vulnerable target group, the activity tandems are purposely organized for a smaller number of older adults. The older adults and mentors of the activity tandems can coordinate the time and location of their weekly meetings flexibly on their own.

### Measures

All participants will complete an assessment at baseline (T1), at the end of the 12-month intervention (T2), and 6 months after the end of the intervention (T3). Before each assessment, participants will be asked to fill out a self-administered questionnaire and, for the detection of objective PA behavior, will be given a pedometer to wear for 7 consecutive days. The questionnaire will assess the older adults’ psychosocial and physical health and evaluate motivational aspects related to PA in a community setting. Sociodemographic information will be assessed within the questionnaire at T1 only, comprising target group-specific items from the German Health Interview and Examination Survey for Adults [49].

Further measurements will take place in communal facilities in the older adults’ neighborhood and will be carried out by qualified staff members. Each assessment will start with the measurement of anthropometric data (height and weight) as well as the registration of current medication intake and existing diagnosed diseases via interview. Using the EQ-5D-3L questionnaire, the participants’ subjectively perceived health status in terms of mobility, self-care, regular daily activities, pain, discomfort, anxiety, and depression will then be determined by interview (3 response options: no problems, some problems, and serious problems) [50]. Additionally, their general self-rated health status will be recorded using the vertical visual analog scale EQ-VAS (1-100) [50].

An additional process evaluation will be performed during the intervention period using questionnaires for participants (after a period of 4 weeks) and mentors (after the workshop, 3 months after the intervention). Furthermore, qualitative interviews and informal notes, reports, and documentation of the PA groups will also be obtained from the activity tandems as well as from group meetings (Table 1 for a summary of outcomes).

**Table 1 table1:** Outcome measurements of the population-based prospective observational cohort study BeTaSen (Bewegungs-Tandems in den Lebenswelten Chemnitzer Seniorinnen und Senioren: ein Beitrag zur kommunalen Gesundheitsförderung). T1 is baseline, T2 is the end of the intervention period (12 months), and T3 is 6 months after the end of the intervention (study population: older adults aged 75 years or older living in Chemnitz, Germany).

Assessment		Instrument or scale	Time of measurement	
**Outcome**				T1, T2, T3
	Physical function	Short Physical Performance Battery (SPPB) Handgrip strength (handgrip dynamometer)		
	Physical activity	OMRON Walking Style One 2.1. Pedometer (7 days) PRISCUS-PAQ		
	Psychosocial health	German Depression Scale (DIA-S) Items of Tilburg Frailty Indicator (TFI) Items of social support questionnaire (F-SozU)		
	Cognitive function	Montreal Cognitive Assessment (MoCA)		
**Process**				
	Feasibility	Documentation of activity tandems and group meetings adherence rates Qualitative interviews and self-administered questionnaire with older adults, mentors, exercise trainers, and communal partners	Each activity tandem or group session Monthly during the activity tandem period and after the end of the individual intervention period (older adults); after the end of intervention in the respective neighborhood (mentors, communal partners)	
	Usefulness	Qualitative interviews and self-administered questionnaire with older adults, mentors, and exercise trainers	Monthly during the activity tandem period and after the end of the individual intervention period (older adults); after the end of intervention in the respective neighborhood (mentors, communal partners)	
	Implementation (barriers and facilitators)	Qualitative interviews and self-administered questionnaire with mentors, exercise trainers, and communal partners	Monthly during the activity tandem period and after the end of the individual intervention period (older adults); after the end of intervention in the respective neighborhood (mentors, communal partners)	

The main activity and health-related outcomes will be addressed in the following subsections.

#### PA Behavior

PA behavior will be objectively assessed using the OMRON walking style one 2.1. pedometer (OMRON Cooperation) that records a person’s steps, walked kilometers, kilocalories used, and aerobic steps per day over 7 consecutive days. Participants will be instructed to wear the pedometer on their hip during waking times as well as get information about the use and purpose of the pedometer. After the pedometer has been returned, the data will be transferred by study assistants to a Microsoft Excel (Microsoft Corporation) spreadsheet. Activity data for days with at least 500 steps will be included for further analysis, according to Meyer et al [51].

For a subjective evaluation of PA behavior, the PRISCUS-Physical Activity Questionnaire (PRISCUS-PAQ) for older adults aged 70 years or older will be assessed based on interviews during T1, T2, and T3 measurements [52]. PRISCUS-PAQ consists of 10 main items on sedentary behavior, daytime naps, cleaning, and other housework, cycling, gymnastics, group exercise, other PA, walks, and gardening. The total score of the PRISCUS-PAQ reflects the individual’s energy expenditure (metabolic equivalent) during the previous week [52].

#### Physical Performance

The digital grip dynamometer (JAMAR Smart Hand Dynamometer; Performance Health Supply Inc) will be used to assess the participants’ handgrip strength. During this test, participants sit upright in a chair without an armrest with their arm bent to 90°. A total of 3 trials are performed per hand, alternating between right and left, with a test duration of 3-5 seconds for each trial. The mean and highest values of the 3 trials for each hand will be analyzed [53]. Additionally, the dominant hand will be queried.

To prove the impact of the exercise intervention on participants physical performance, the widely used, highly reliable, and valid Short Physical Performance Battery (SPPB) will be used [54]. The SPPB includes balance (Romberg, Semi-Tandem, and Tandem), gait speed (4-meter walk), and chair rise tests. Each of these 3 SPPB components is scored from 0 (inability to carry out) to 4 (best performance). There is a potential range between 0 and 12, with higher scores indicating higher functional performance. Participants with cut-off points of less than or equal to 6 points will be classified as “poor performers.” Whereas a score of 7-9 points will define the “moderate performers,” and the “good performers” will have scores of 9 points or more [55]. In a systematic review and meta-analysis, the SPPB has been shown to be a predictive tool for all-cause mortality [56].

The 2-minute step test (TMST) [57] will be used to assess the participants’ endurance capacity. The test starts with a 2-minute rest period. Participants will then stand in front of a wall and raise their thigh to be horizontal to the floor; a mark (strip) will be placed in the position corresponding to the middle of their thigh bone, between the kneecap and frontal prominent pelvis bone. Participants will be instructed to alternately lift their knees as often as they can over a 2-minute period, such that their knees reach the marked location. After completing the TMST, the researcher will record the participants’ number of steps, or “steps,” as an outcome measure. Before the start of the test, directly after, and 30 seconds after the end of the test, the participant’s heart rate in beats per minute and measurement of oxygen saturation in percent (through a pulse oximeter) as well as a subjective rating of perceived exertion (through the Borg scale [48]) will be recorded.

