Qualitative interviews and focus group discussions will be protocolized by researchers and audio recorded, which will be transcribed afterwards. Qualitative data will be analyzed using a qualitative content analysis, according to Mayring and Fenzl [62], with the aim of structured processing of the material by coding relevant interview passages deductively in a theory-driven system of categories. Frequent text material that cannot be assigned to a deductive main category will result in the creation of new (inductive) main categories or subcategories [62]. The coding scheme will subsequently be supplemented with additional categories that emerge from the text material. These newly added categories will either be treated as subcategories of already existing categories or as new main categories. The text material will be coded with the help of MAXQDA (VERBI GmbH).

For this pilot study in the municipal area, the number of participants was calculated based on the project period and the project funding type in terms of feasibility within the study period.

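### The SPPB performance bands overlap at one score: a total of 9 is both moderate and good, so those two groups are not uniquely defined

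*Protocol article*

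**What the plan says.** The scoring rule and the bands are in the protocol article, Methods, Physical Performance. On the components: "Each of these 3 SPPB components is scored from 0 (inability to carry out) to 4 (best performance". On the total: "There is a potential range between 0 and 12, with higher scores indicating higher functional performance".

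Three classes are then defined on that total, with one citation (reference 55):

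- Poor: "Participants with cut-off points of less than or equal to 6 points will be classified as “poor performers".
- Moderate: "a score of 7-9 points will define the “moderate performers".
- Good: these participants "will have scores of 9 points or more".

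The bands are not restated anywhere else. Table 1 lists the SPPB only as an instrument for physical function, measured at T1, T2 and T3. The Statistical Analysis section does not mention the SPPB classes.

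**The concern.** A classification rule should place every possible score in one class and only one. Here the upper end of the moderate band and the lower end of the good band are the same number, and both ends are inclusive. A participant with 9 points satisfies both definitions, and no tie rule is given.

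The rule is stated as something that will be done to participants, not as background on the instrument. Any table that counts moderate and good performers, and any comparison that groups people by these bands, therefore needs a decision that the text does not make. All participants receive the intervention and there is no randomised control group, so the evidence on impact comes from change over time. If the boundary were chosen after the data had been seen, the number of people reported as moving into the good class could depend on that choice.

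**Working it through.** **Inputs** (all from Physical Performance, except the last):

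- Three components, each scored 0 to 4, so the total runs from 0 to 3 × 4 = 12, giving 13 possible integer totals. This reproduces the stated range.
- Poor: total ≤ 6. Moderate: 7 ≤ total ≤ 9. Good: total ≥ 9.
- Planned number of participants: about 120 (Design and Organization of a Physical Activity–Promoting Intervention).

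**Step 1: count the bands that each total falls in.**

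| Total | Bands met | Number of bands |
|---|---|---|
| 0-6 | poor | 1 |
| 7-8 | moderate | 1 |
| 9 | moderate and good | 2 |
| 10-12 | good | 1 |

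Twelve totals are classified once, one is classified twice, and none is left out.

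**Step 2: check that a total of 9 can occur.** Three component scores from 0 to 4 give 5 × 5 × 5 = 125 combinations. Those summing to 9 are 3+3+3 (1 way), 4+3+2 (6 orders) and 4+4+1 (3 orders), so 1 + 6 + 3 = 10. This shows only that 9 is attainable; it is not an estimate of how often it occurs.

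**Step 3: check the possible repairs.** Moderate 7-8 with good 9-12, and moderate 7-9 with good 10-12, each put all 13 totals in exactly one band. Internal consistency does not favour either.

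**Step 4: size at one visit.** Let p be the proportion scoring exactly 9 at that visit.

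- Share good under the first reading: P(total ≥ 9).
- Share good under the second reading: P(total ≥ 10).
- Difference: P(total ≥ 9) − P(total ≥ 10) = p.

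The article gives no SPPB distribution, so p is an assumption:

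| Assumed p | People out of 120 | Difference in share good |
|---|---|---|
| 5% | 0.05 × 120 = 6 | 5 percentage points |
| 10% | 0.10 × 120 = 12 | 10 percentage points |
| 20% | 0.20 × 120 = 24 | 20 percentage points |

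**Step 5: size for change between visits.** With one reading used throughout, the T1-to-T2 change in the share good differs between the readings by p at T2 minus p at T1. That is a net difference and may be close to zero. For one person, a move from 8 to 9 is an upgrade under the first reading and no change under the second; a move from 9 to 10 is the reverse.

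**Comparison within the article.** The MoCA bands in the Cognitive Function section (below 19, 19-25, 26-30) put every score from 0 to 30 in exactly one class. The overlap is therefore specific to the SPPB.

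**The case against.** The strongest reply is that little in the article depends on these bands. The Statistical Analysis section names no analysis by SPPB class. Its example grouping variables are age, gender, vulnerability and sociodemographic factors, and the research questions add previous disease. Those lists are open-ended, but none includes the SPPB bands. The 0-12 total remains available for any analysis of change and is untouched. The article also describes the sample size as feasibility-driven: "the number of participants was calculated based on the project period and the project funding type in terms of feasibility within the study period". No eligibility rule, sample size or named test uses the boundary. All of this stands, and it keeps the point minor.

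Three stronger readings are tempting, and the document does not support them.

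- A reader might infer that the whole classification is unusable. It is not: only a total of 9 is ambiguous.
- A reader might infer that someone who stays at 9 could be counted as moderate at T1 and good at T2. That needs different cut-offs at different visits, and nothing in the article suggests this. Under either single reading an unchanged score stays in the same class.
- A reader might take the percentage points in the illustration as bias in the intervention effect. They are a difference in a share at one visit, under an assumed proportion. The effect on change is the net difference in Step 5, which cannot be estimated from the article. Although the SPPB is introduced as the measure of impact on physical performance, nothing says that impact will be judged by band.

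The reply does not remove the overlap. The article chose to state the rule, and the rule contradicts itself. This is not a detail left to a fuller document.

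**Conclusion.** The point holds in a limited form: the bands are wrong as written, and the severity is minor. A total of 9 belongs to both the moderate and the good class, so the counts in those two classes, and any grouping based on them, are not uniquely defined. The poor class, the other 12 totals and the 0-12 score are unaffected.

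At any visit the share of good performers differs between the two readings by exactly the proportion scoring 9. That identity needs no assumption. The figure of 6 to 24 people does: it rests on an assumed 5% to 20% of 120 participants and is illustrative only.

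The article does not show which boundary is intended, and the cited source is not available here, so neither reading can be called the correct one.

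**What to change.** Check the two cut-offs against the source cited for them (reference 55) and correct one number so that the bands are mutually exclusive: either moderate 7-8 with good 9-12, or moderate 7-9 with good 10-12. Record the choice before the SPPB data are analysed, and apply the same bands at T1, T2 and T3. If any T1 table by SPPB class has already been produced, state which boundary it used.

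The cost is one number in the text and one look at the cited source. No data collection, measurement or sample size changes.
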